### **6.2 ( $^{18}\text{F}$ ) CETO**

To date this has been administered to nine patients with secretory and non-secretory adrenocortical tumours. It has also been extensively studied ex vivo in a range of secretory adrenal adenomas and carcinomas. Specific [ $^{18}\text{F}$ ]CETO uptake was elevated in aldosterone-producing adenomas of all three mutation types (KCNJ5, ATP2B3 and CACNAID). Specific uptake in human- and NHP spleen was lower than in normal adrenal gland and APAs, Specific uptake in PCC, small intestine and kidney was also lower than normal adrenal gland, as was liver uptake

(compared to normal, mutated as well as pathological adrenal gland). [18F]CETO tissue-to-adrenal gland ratio showed a threefold uptake in APAs compared to normal adrenal gland. (WBIC, 2019, Investigator Brochure, V1).

As with 11C-metomidate, its specificity in vivo for CYP11B2 (encoding the enzyme for aldosterone synthesis) is expected to require temporary suppression of cortisol synthesis, by 72 hours of pretreatment by dexamethasone. In this and most other respects the protocol for administration of 18F-CETO will be as for 11C-metomidate, as above. There are two exceptions:

[i] The longer half-life allows patients to be scanned (pictured) at multiple timepoints after a single injection of radioisotope; patients who are able to stay (upto 5 hours) will be invited to have more than one scan (picture), exploring the flexibility and convenience this may provide in the future.

The radiation exposure is, of course, the same whether patients have one or several scans (pictures) after an injection

[ii] Serum cortisol will be measured both at the time of the scan (as for 11C-metomidate) and on the day after the scan, whenever this is logistically possible.

## **6.2 Adrenal Vein Sampling**

This test is currently the gold standard diagnostic technique for diagnosing Conn's adenoma. The test is carried out in the radiology department by a specialist radiologist. During the first two hours the patient will be cannulated and ACTH (Adrenocorticotrophic hormone) infused in 0.9% saline for 3 hours approximately, commencing half an hour before and continued during the procedure. This is routinely used in the AVS procedure to stimulate the adrenal glands. This maximises the chances of detecting a difference between the two glands and aldosterone production. This is a common clinical diagnostic test in clinical practice.

A small cannulae and catheter are introduced via the groin (usually into the right) to access the blood vessels by the radiologist. Through the needle the catheter is introduced and then positioned in adrenal gland veins. The blood samples from both adrenal veins, and the main vein (inferior vena cava) are used to measure the levels of adrenal hormones, aldosterone and cortisol, and metanephrines. These are routine measurements in the AVS procedure, the current gold standard. [Extra blood for experimental measurements such as cell-free DNA, and DPP4 will be taken]. Blood which is not used for these assays will be kept frozen for the development of future tests which may improve our ability to predict outcome from adrenalectomy. These are likely to be additional steroids, secreted proteins, or cell-free RNA or DNA.

Post procedure, patients are to lay flat. During this time, the right groin is routinely inspected to make sure there is no oozing from the site or any significant bruising. Blood pressure and heart rates are monitored. Patient will be discharged by radiologist. The risk of the procedure we are looking to minimise here is excessive bleeding or haemorrhage afterward. This is rare. There is a potential, although very rare of an adrenal infarction.

## **7.0 Cardiac Magnetic Resonance Imaging Scan (CMR)**

All patients will be invited to have a cardiovascular magnetic resonance scan (CMR) at baseline visit which will be repeated at the 6-12 months' time point, following baseline visit. There is an expectation that not all patients will consent to this optional measurement.

CMR uses a powerful magnet and radio waves to form pictures of the heart. Gadolinium-based intravenous MR contrast will be administered via an intravenous cannula for angiography, myocardial perfusion and viability. The incidence of developing adverse events following administration is very low. Most reactions are mild and include warmth, coldness and pain at cannula site, headache, vomiting, paraesthesias, dizziness and itching. Very rarely, between 0.001% to 0.01% an anaphylactoid reaction may occur. The CMR suite, at St Bartholomew's NHS Trust, have trained clinical staff to manage this condition if it should occur. Patients will have renal function blood tests prior to scan. Patients will be requested to arrive approximately 30 minutes before the actual scan appointment time to perform a brief assessment and change into a gown. The scan itself takes about forty minutes. It involves patient lying in supine position inside a large open-ended tube. Electrocardiogram monitoring will continue during the scan. Patients will be asked to hold breath between 2 and 15 seconds prior to image capture. Patients will be able to communicate the operator anytime via telecon.

## **8.0 Sub-study of Repeat Metomidate PET CT before and after Spironolactone/eplerenone therapy**

In order to determine whether it will be necessary for the start of spironolactone/eplerenone treatment to be delayed in all patients until after both investigations are completed, we will perform a sub-study, early in MATCH, in which 6 patients have their PET CT repeated at least after 6 weeks treatment with spironolactone/eplerenone. (This is the conventional period of time for which spironolactone is withdrawn prior to AVS.)

## **9.0 Follow-up management and investigations**

We anticipate ~50% of patients will be found on one or both investigations to have unilateral PA, and be recommended for adrenalectomy. The primary outcome measurements will be at 6 months after surgery.

### **9.1 Stopping Criteria**

Withdrawal criteria for individual patients are shown in section 4.1 page 26 below. Criteria for the whole trial will be determined by the Trial Steering Committee (TSC), or delegated (if deemed appropriate by the TSC) to an independent DMEC (see [12]). Because neither technique is new, it is highly unlikely that any stringent safety boundary that is set will be crossed. Any stopping rules will need to acknowledge that there is a long lag between the interventions and the assessment of outcome: at least 9 months, given the 6-month post-operative timing of primary assessment, the interval between diagnostic intervention and surgery, and frequency of the endpoint committee assessments.

## 9.2 Study population

The potential constituency of patients at which MATCH is directed is the majority of all patients with PHA who indicate a desire to proceed to surgery if lateralisation can be confidently shown. The diagnostic criteria for PHA used in all participating centres will be drawn from the recently published updated Endocrine Society consensus guidelines (2016).(31) All patients will have had standard cross-sectional imaging by CT or MR scanning. If patients have had 11- C Metomidate scan and AVS with or without baseline visit they will be included in ITT analysis

## **10.0 Inclusion/Exclusion criteria:**

### **10.1 Inclusion Criteria**

- Male or female: Age >18 yrs.
- Diagnosis of PHA based on current published Endocrine Society consensus guidelines (Funder et al 2016)

- **Patients will be enrolled/consented when they have had each of the following:**

At least one paired measurement of plasma renin and aldosterone, measured off spironolactone/eplerenone and other polluting medications, showing an elevated ARR and.

1. *either* a plasma aldosterone >190 pmol/L after saline infusion
2. *or* 'spontaneous hypokalemia + plasma renin below detection levels + plasma aldosterone > 550 pmol/L)' (as per Endocrine Society guidance, 2016)
3. *or* failure to suppress plasma aldosterone by 30% + persistent PRA suppression after oral administration of captopril (as per Endocrine Society guidance, 2016)

**and** a CT or MRI scan of the adrenals with probable or definite adenoma(s) within the last five years

- Patients with elevated ARR can be put forward for consideration by the MDT as exceptional cases in whom spironolactone/eplerenone is not (fully) withdrawn, and/or saline suppression is not performed, IF:
  1. Plasma Aldosterone > 450 pmol/L **AND** plasma renin <0.5 pmol/ml/hr (<9 mU/L) if measured on treatment with ACEI (Lisinopril ≥20 mg or equivalent) or ARB (Losartan 100 mg or equivalent); OR

## 2. Age <40 AND definite adrenal adenoma on CT or MRI

**Patients whose CT/MRI does not show probable or definite adenoma must also be reviewed by MDT before enrolment/consent**

- All patients will have a positive Aldosterone renin ratio (ARR) serum measurement with another local diagnostic confirmatory test as specified from local specialised APA Guidelines. This is often standard cross-sectional imaging by CT or MR scanning. Any exception to recommended diagnostic criteria will be subject to approval by monthly MDT.

### 10.2 Exclusion Criteria

- Those patients who indicate that they are unlikely to proceed with surgery will not be recruited, because there will be no outcome change in blood pressure, restoration of normal renin/angiotensin physiology) against which to compare the accuracy of the two Investigations. Patients contraindicated for spironolactone/eplerenone therapy use.
- Any patients continuing on beta-blockers or direct renin blockers.
- Pregnant patients or women unable/unwilling to take secure contraceptive precautions whilst undergoing investigation.
- Patients unwilling/unable to take the dexamethasone required to prepare for a metomidate PET-CT scan
- Patients unwilling to have both 11- C Metomidate PET CT/ scan and Adrenal Vein Sampling.
- Any illness, condition or drug regimen that is considered a contraindication by the PI

NB: Patients unable to have baseline cardiac MRI due to claustrophobia per se may still be to included in the MATCH study at the PI discretion.

All other patients with PHA however, are potential candidates for inclusion in MATCH, including those with apparently normal bilateral adrenal morphology, given that small APAs lying within the body of the adrenal may not be seen on even high resolution CT scanning.

### 10.3 Withdrawal Criteria

Unwillingness or inability to undergo both PET CT and AVS or at the PI discretion.

## **11.0 Diagnostic Investigations**

The primary control intervention is AVS and will be performed according to an identical protocol

at all centres whose internal audit data indicate a successful bilateral cannulation rate of >75%. Briefly, the femoral vein is cannulated under local anaesthesia and catheters advanced under fluoroscopic guidance into each adrenal vein.(17) The procedure is performed under conditions of ACTH stimulation, which facilitates unequivocal confirmation of secure adrenal vein cannulation. Blood samples from both adrenal veins and the lower part of the inferior vena cava are analysed for aldosterone (A) and cortisol (C) and an aldosterone/cortisol (A/C) ratio calculated at each site. Lateralisation (providing evidence for an adrenalectomy to be recommended) is deemed to exist if the A/C value in one adrenal vein is at least 4-fold higher than the other. In preparation for AVS, treatment to control blood pressure is limited to a non-dihydropyridine calcium antagonist (e.g. verapamil) and doxazosin (together with potassium supplementation as needed), as the treatments least likely to interfere with interpretation of aldosterone/renin measurements. Although some rise in blood pressure is permitted in preparation for AVS, severely hypertensive patients may require additional therapy according to clinical judgement.

The experimental intervention is  $^{11}\text{C}$ -metomidate PET-CT. There has been no change in the protocol used since the proof-of-concept study. Patients are treated with dexamethasone 0.5 mg 6-hourly for 3 days, then receive an injection of 250 mBq (on average) of  $^{11}\text{C}$ -metomidate, with CT and PET scanning of the adrenal area 20-30 minutes later. A positive (lateralization) result is indicated by a maximum standardised uptake at least 25% greater in one adrenal gland compared to the other.

The assessment of the two diagnostic modalities will be undertaken at a monthly MDT of endocrinologists and radiologists. Patients will be offered surgery if one or both techniques indicate unilateral disease. For the very small number of cases (we estimate 1 in 25 on the basis of the proof-of-concept study), where AVS and  $^{11}\text{C}$ -metomidate PET-CT each meet these criteria for lateralisation, but to opposite sides, we will defer to the Trial Steering Committee (TSC) (see section 11).

The primary outcome is cure of PHA by unilateral adrenalectomy and will be determined by an endpoint committee blind to results of the prior imaging tests.

The secondary intervention is a systematic evaluation of spironolactone eplerenone therapy, as a predictor of primary or secondary outcomes. After both diagnostic investigations (AVS and  $^{11}\text{C}$ -metomidate PET-CT) have been performed, spironolactone/eplerenone will be prescribed in a standardised fashion with home blood pressure monitoring before and after four weeks of treatment (50 mg/day for two weeks, force-titrated to 100 mg/day after two weeks unless SBP is <130 mmHg on repeat home monitoring, and/or plasma K+ is >5.0).

In addition to the clinical interventions, we plan a number of laboratory procedures to confirm that the adenoma(s) removed at surgery were aldosterone-secreting, and to look for genetic and/or biochemical differences between APAs. These differences, if observed, will then be correlated with either prior differences in the  $^{11}\text{C}$ -metomidate PET-CT signal and/or the subsequent outcome from surgery. The techniques for these laboratory procedures (immunohistochemistry for CYP11B1 and CYP11B2, qPCR for *CYP11B1*, *CYP11B2*, *CYP17A1*, and primary cell culture for measurement of aldosterone secretion) are all well-established in our laboratory. Targeted sequencing of genes with known somatic mutations will also be performed, as described above.

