| 
11-Cmetomidate PET CT scan/Adrenal Vein sampling
 | 
 
• If patient is on a MR (spironolactone/eplerenone antagonist this will usually need to be stopped 6 weeks before going onto AVS sampling.
 
• Correct potassium depletion following local guidelines.
 
• Patient enrolled onto Ecrf with PET CT and AVS order of allocation determined by minimisation
 
 
Prior to 11-C-metomidate PET CT and [18F]CETO,PET CT scan:
 
 
• 0.5mg Dexamethasone to be taken 6hrly 3-5 days before scan
 
 
Prior to AVS:
 
 
• Spironolactone/eplerenone will usually be stopped 6 weeks before;
 
• Correct potassium depletion, following local guidelines. Bloods for ACTH, cortisol, electrolytes with bicarbonate, urea, creatinine, plasma renin mass and aldosterone
 
 
Treatment:
 
 
• 11-C metomidatePET CT scan and AVS results reviewed at specialist MDT 
 
○ If lateralisation occurs, patient informed and referred for adrenalectomy
 
○ Post-operative analyses of aldosterone-producing adenoma (genotyping and somatic mutations)
 
 
 
• All patients continue/commence treatment with spironolactone/eplerenone
 
 |

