## **21.0 Planned Methods of Analysis**

The planned study analyses will be detailed in the study-specific Statistical Analysis Plan (SAP), which will be finalised in advance of study closure.

The primary outcomes will be analysed in a hierarchical manner:

1. Change in ARR, between baseline and 6 months post-surgery (or equivalent time-point relative to baseline if no surgery), comparing patients who have surgery with patients who do not have surgery.
2. Blood pressure cure rates (home SBP < 135 mmHg on no antihypertensive treatment), comparing patients who have surgery with patients who do not have surgery.
3. ARR in patients who have surgery but have discordant AVS and PET-CT results, comparing patients whose surgery was indicated by high probability PET CT with patients whose surgery was indicated by high-probability AVS.
4. Blood pressure cure-or-control rates (home SBP =20 mm Hg or DBP =10 mm Hg lower than prespironolactone/eplerenone, i.e. baseline) in patients with discordant AVS and PET-CT results, comparing those whose surgery was indicated by high-probability PET CT with patients whose surgery was indicated by high-probability AVS.

5. Blood pressure cure rates (home SBP < 135 mmHg on no antihypertensive treatment) in patients with discordant AVS and PET-CT results, comparing those whose surgery was indicated by high-probability PET CT with patients whose surgery was indicated by high-probability AVS.

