### **24.3 Critical Endpoints Committee**

This will consist at least one physician (Endocrinologist and/or Hypertension specialist), at least one Pathologist and a PET Nuclear Medicine Specialist. They will be independent of those involved in the patients' care, including the pre-operative and post-operative assessments. They will assess the pre-operative investigations (AVS and PET CT) without knowledge of outcome from surgery, and vice versa. This committee will meet every 3-6 months.

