### 2.2.3. 11C-METOMIDATE PET-CT

For the FAS, whether dexamethasone was taken for 3-5 days prior to the scan will be summarised; where this has not occurred, the reasons will be summarised and/or listed.

For the FAS, the following laboratory measures will be summarised as a whole, and in relation to whether the 11C-Metomidate PET-CT results indicated BAH, unilateral APA (left), unilateral APA (right), or were inconclusive:

- Sodium, potassium, creatinine, eGFR, urea, bicarbonate, renin mass, renin activity, aldosterone, aldosterone renin ratio (ARR), serum cortisol, serum ACTH

For the FAS, the following 11C-Metomidate PET-CT measures will be summarised as a whole, and in relation to whether the results indicated BAH, unilateral APA (left), unilateral APA (right), or were inconclusive:

- Right Adrenal
  - Number of possible tumours
  - Mean tumour diameter
  - Maximum standardised uptake value (SUVmax) over all tumours, (calculated by TOF and SharpIR)
  - SUVmax over the normal adrenal (TOF and SharpIR)
  - Ratio of SUVmax over tumour to SUVmax over normal adrenal (TOF)
  - Ratio of SUVmax over tumour to SUVmax over normal adrenal (SharpIR)
  - Probability of adrenal adenoma
- Left Adrenal
  - Number of possible tumours
  - Mean tumour diameter
  - Maximum standardised uptake value (SUVmax) over all tumours, (calculated by TOF and SharpIR)
  - SUVmax over the normal adrenal (TOF and SharpIR)
  - Ratio of SUVmax over tumour to SUVmax over normal adrenal (TOF)
  - Ratio of SUVmax over tumour to SUVmax over normal adrenal (SharpIR)
  - Probability of adrenal adenoma
- SUVmax over liver (TOF and SharpIR)
- Overall Probability of Unilateral Aldosterone Producing Adenoma

For the Substudy Population, these same measures will be summarised for scans performed whilst taking spironolactone, and when off spironolactone. Bland-Altman plots and cross-tabulations will be used to assess the level of agreement between scans.

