## **2.3. EFFICACY OUTCOMES**

### **2.3.1. PRIMARY OUTCOMES**

The primary outcomes will be analysed hierarchically. If the first primary analysis is statistically significant at  $p < 0.05$ , then the second primary outcome will be analysed; if the second primary analysis is statistically significant at  $p < 0.05$ , then the second primary outcome will be analysed; and so on. If any primary analysis fails to reach  $p < 0.05$ , then subsequent analyses will be considered secondary analyses.

Each primary outcome will be analysed in the subgroup of FAS patients who undergo surgery.

- Cure of hypertension at 6 months (non-inferiority analyses)
  - comparing accuracy of AVS and 11C-Metomidate PET-CT
  - each scan judged to be accurate if it indicated unilateral disease and cure of hypertension was achieved after surgery, or if the scan did not indicate unilateral disease and cure was not achieved after surgery
  - report estimated difference in accuracy (Newcombe-Wilson method for paired data) between 11C-Metomidate PET-CT and AVS, with 95% CI
  - non inferiority of 11C-Metomidate PET-CT will be declared if the lower limit of the above 95% CI is greater than -17%
  - each measure of cure (see Section 1.8) will be analysed in turn
- Cure of hypertension at 6 months (superiority analyses)
  - in addition to above, report p-value from exact McNemar test
  - superiority of 11C-Metomidate PET-CT will be declared if  $p < 0.05$ , and the lower limit of the 95% CI is greater than 0%

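### Neither PET-CT nor AVS is masked to the other, and SAP 2.3.1 does not say whose call or which rule counts as indicating unilateral disease, so the paired comparison is open to drift toward agreement

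*Combined protocol and SAP*

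**What the plan says.** **Assessment and masking.** The protocol synopsis has "11-C metomidatePET CT scan and AVS results reviewed at specialist MDT", and section 11.0 has "The assessment of the two diagnostic modalities will be undertaken at a monthly MDT of endocrinologists and radiologists". Section 11.0 also has the outcome judged by a committee blind to the test results. Section 24.3 says of the Critical Endpoints Committee: "They will assess the pre-operative investigations (AVS and PET CT) without knowledge of outcome from surgery, and vice versa". No section masks PET-CT to AVS or AVS to PET-CT. None says whether the MDT's or the committee's classification enters the analysis. Section 19.0 balances test order by minimisation, with override allowed, so AVS should come first in roughly half of patients.

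**PET-CT call.** Section 11.0: "A positive (lateralization) result is indicated by a maximum standardised uptake at least 25% greater in one adrenal gland compared to the other". SAP 2.2.3 groups PET-CT results into bilateral, unilateral left, unilateral right or inconclusive. It lists "Overall Probability of Unilateral Aldosterone Producing Adenoma" with no scale or cut-off, and records SUVmax under two reconstructions (TOF and SharpIR).

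**AVS call.** Section 11.0 deems lateralisation to exist "if the A/C value in one adrenal vein is at least 4-fold higher than the other". Section 4.2 describes a 4-fold ratio together with contralateral suppression relative to the IVC, and an equivocal zone between 2 and 4. SAP 2.2.2 also has an inconclusive category.

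**Primary analysis.** SAP 2.3.1: "each scan judged to be accurate if it indicated unilateral disease and cure of hypertension was achieved after surgery", or if it did not indicate unilateral disease and cure was not achieved. Non-inferiority needs the lower 95% limit for PET-CT minus AVS to exceed -17 points.

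**The concern.** In a paired accuracy study the information lies in the pairs where one test is right and the other wrong. If the person making one call can see the other test's result, an equivocal reading can be settled in its favour. A discordant pair then becomes concordant, and the measured difference no longer describes two independent tests. Masking tests to outcome does not prevent this.

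The opening is wider because the call itself is not pinned down. For a valid scan, a 25% asymmetry rule gives positive or negative; it cannot by itself give an inconclusive result, and it is not linked to the probability fields or to one reconstruction. AVS has the same kind of gap. Loss of discordance is most harmful to a non-inferiority claim, because moving both tests toward agreement moves the difference toward zero and away from the margin.

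**Working it through.** **1. The plan's own figures (protocol section 33.0; SAP 1.5).**
- Pairs favouring PET-CT: D+H+I+O+Q = 10 + 9 + 0.5 + 0.25 + 0.25 = 20% of patients.
- Pairs favouring AVS: G+J+M+P = 1 + 3.5 + 0.25 + 0.25 = 5%.
- p = 20/25 = 80% and the discordant share is 25%, as stated.
- Operated: C+D+G+H+I+J+K+L+M+O+P+Q = 56%.
- PET-CT accuracy: (D+H+I+L+O+Q)/56 = 49/56 = 87.5%. AVS: (G+J+L+M+P)/56 = 34/56 = 60.7%. Difference: 15/56 = +26.8 points.
- Under the SAP wording cell C would also count as AVS correct, giving AVS 35/56 = 62.5%. The protocol's formula is kept below.

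**2. Switching on that table.** Let f be the share of conflicting PET-CT reads changed to the AVS answer. The documents give no value, so f is an assumption.
- *One-way* (only PET bilateral/AVS unilateral, cells I and J): PET-CT gains 3.5f and loses 0.5f, so the difference is (15 + 3f)/56.
- *Two-way* (also PET unilateral/AVS bilateral, cells G and H): after switching, neither test indicates surgery, so 10f leave the operated set. PET-CT correct = 49 + 3f - 9f; AVS correct = 34 - f; difference = (15 - 5f)/(56 - 10f).

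| f | One-way | Two-way |
|---|---|---|
| 0 | +26.8 | +26.8 |
| 10% | +27.3 | +26.4 |
| 25% | +28.1 | +25.7 |
| 50% | +29.5 | +24.5 |
| 100% | +32.1 | +21.7 |

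**3. Switching when the truth is at the margin.** The SAP rule (Newcombe paired 95% CI, lower limit above -17 points) was simulated with:
- a true difference of -17 points;
- n = 70 (the minimum number of adrenalectomies in protocol 12.1) or n = 92 (56% of 165);
- 25%, 35% or 45% of pairs discordant (assumed);
- 85% of concordant pairs both correct (assumed);
- two-way switching, with switched patients kept in the analysis (a simplification).

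The measured difference becomes -17(1 - f): -15.3, -12.75 and -8.5 points at f = 10%, 25% and 50%.

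| f | False non-inferiority, range over n and discordance |
|---|---|
| 0 | 2.6-2.7% |
| 10% | 4.5-5.9% |
| 25% | about 10-16% |
| 50% | 33-59% |

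**4. Superiority.** With equal true accuracies and one-way switching only (25% or 45% discordant, same n), superiority is declared in 1.4-1.9% of trials at f = 0, 2.5-3.8% at 10%, 4.8-10.0% at 25% and 15-39% at 50%. This result depends on switching being one-sided.

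**The case against.** The strongest reply is that section 11.0 does tie the calls to numbers. Right after the MDT sentence it speaks of both tests meeting the criteria just given, which are the 25% and 4-fold rules. The probability field is one line in a descriptive list. The protocol's analysis wording, "comparing patients whose surgery was indicated by high probability PET CT with patients whose surgery was indicated by high-probability AVS", belongs to a hierarchy that the SAP says it departs from (SAP 1.10.3 and 1.10.4). SAP 2.3.2 names SharpIR for a tumour-to-contralateral ratio, and SAP 2.2.7 implies that a separate diagnosis is recorded for each test. SAP 2.3.4 already plans to explore other thresholds.

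Much of this stands. It rules out three readings that a reader might infer:
- *That PET-CT is scored on a subjective scale that replaces the 25% rule.* No section says so; undefined and unreconciled is all that the text supports.
- *That the endpoints committee reads the two tests side by side.* Section 24.3 says only that it assesses both without knowing the outcome.
- *That only PET-CT can drift.* AVS has its own undefined high-probability label, an inconclusive category, a second criterion and a grey zone.

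The gap remains. SAP 2.3.1 does not refer to the section 11.0 rules, the SharpIR ratio is listed as a predictor and not as the call, and nothing says who enters each call or when. The exploratory thresholds do not define the primary call. The only sensitivity analysis (SAP 2.3.6) removes AVS technical failures and would not reveal borrowing.

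**Conclusion.** The point holds as a gap in masking and definition that affects both tests. Borrowing is possible; the documents do not show that it occurs.

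Its size depends on f. Near the -17 point margin, which is the case a non-inferiority test must guard against, f = 25% takes the false-claim rate from about 2.6% to about 10-16%, under the simulation assumptions listed.

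A reader might go further and conclude that the arrangement always favours PET-CT. The protocol's own table does not support that: two-way switching narrows PET-CT's lead from 26.8 to as little as 21.7 points, and only one-way switching widens it, to at most 32.1. With a lead that large, neither pattern would by itself overturn the conclusion. Half of the 20 points favouring PET-CT also sit in cell D, where AVS failed and there is no AVS answer to adopt.

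**What to change.** 1. **SAP 2.3.1.** Name the reader and the rule behind each test's call, how an inconclusive result is scored, and the one SUVmax reconstruction used. First reconcile protocol sections 4.2 and 11.0 with SAP 2.2.2 and 2.2.3. Which criterion is right is for the investigators to settle.
2. **Patients still to be read.** Have the existing reader enter and lock each test's call in the eCRF before the other test's result is opened.
3. **All patients.** Pre-specify a sensitivity analysis of the primary comparison with both calls derived by the data centre from recorded SUVmax and A/C values under the stated section 11.0 criteria.

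The numeric calls belong in a sensitivity analysis because, as the primary call, they could separate the analysed result from the one that led to surgery and leave operated patients negative on both tests.

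**Cost.** SAP text, a locked eCRF entry and a few derived variables from data already listed for collection; no extra reader. Some equivocal results will be called by a number in the sensitivity analysis. SUVmax depends on how the reader marks tumour and normal gland, so values already measured unmasked remain a limitation to report.
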